## Abstract

**Background:**

Water, sanitation and hygiene (WASH) interventions represent an important component of soil-transmitted helminth (STH) infection control, alongside the administration of anthelmintic drugs, which are generally targeted to school-aged children. Recent modelling studies have suggested that STH control programmes should be broadened to include all age groups across the community. We describe the protocol for a pilot study investigating the impact of school-versus-community-based delivery of integrated WASH and deworming programmes on STH infections in school-aged children in Timor-Leste.

**Methods:**

The (S)WASH-D for Worms pilot is a two-arm, non-randomised cluster intervention study. The aims are to determine feasibility and acceptability of the intervention and study procedures and to establish proof of principle for the hypothesis that STH control programmes directed to the entire community will lead to greater reductions in STH infections in children than programmes directed only to school-aged children. Of the six participating communities, three receive a school-based integrated WASH and deworming programme and three additionally receive a community-based integrated WASH and deworming programme. The primary outcomes are the proportions of eligible children who enrol in the study and participate in the data collection, and outcomes relating to WASH and deworming programme completion, coverage, and use. Secondary outcomes are the cumulative incidence and mean intensity of STH infection in school-aged children at 6-month follow-up, mean haemoglobin concentration and several anthropometric indices. Results will inform the design of a cluster-randomised controlled trial (RCT).

**Discussion:**

This pilot study is being conducted in preparation for a cluster-RCT investigating the differential impact of school- and community-based integrated STH control programmes on STH infections in school-aged children. It aims to establish feasibility and proof of principle, while results of the subsequent RCT could have significant implications for global STH control policy.

**Trial registration:**

Australian New Zealand Clinical Trials Registry, ACTRN12615001012561

**Electronic supplementary material:**

The online version of this article (doi:10.1186/s40814-016-0109-4) contains supplementary material, which is available to authorized users.

## Background

Soil-transmitted helminths (STHs) represent a group of parasitic nematode worms which fall into the category of neglected tropical diseases—a group of infections which predominantly affect people living in extreme poverty [1]. The soil-transmitted helminths include hookworms (*Necator americanus* and *Ancylostoma duodenale*), roundworms (*Ascaris lumbricoides*) and whipworms (*Trichuris trichiura*). Together, it is estimated that approximately 1.45 billion people worldwide are infected with at least one of these species of worms [2], with an estimated disease burden in excess of five million disability-adjusted life years (DALYs) [3].

STH infections are transmitted when helminth eggs are excreted in the faeces of infected individuals, contaminating soil in areas without adequate sanitation. Infections are subsequently acquired through direct penetration of the skin by hookworm larvae, or accidental ingestion of *A. lumbricoides* or *T. trichiura* eggs, or hookworm larvae [4]. These infectious stages of STH can remain viable in soil for a period of time ranging from several weeks for hookworm larvae to several years for *A. lumbricoides* eggs [5–7].

Chronic STH infections result in malabsorption of nutrients and micronutrients, and a number of studies show evidence for malnutrition, iron-deficiency anaemia, poor growth and impaired cognitive development in STH-infected individuals [8–14], with children harbouring the largest burden of morbidity [4, 7, 15, 16]. Both *A. lumbricoides* and *T. trichiura* infections have a peak incidence and intensity in children between the ages of 5 and 15, with a decline in both frequency and intensity in adulthood [4]. Hookworm infections, on the other hand, tend to maintain a high prevalence and intensity in adulthood [4, 5]. Despite this, children, along with women of child-bearing age, remain at the highest risk of hookworm-associated anaemia and other related morbidities [5, 17].

Regular treatment with the benzimidazole anthelmintic albendazole leads to rapid and significant decreases in STH prevalence, particularly *A. lumbricoides* and hookworm [18]. Regular anthelmintic delivery—also known as deworming—has been shown in a number of studies to improve STH morbidity indicators, including growth, anaemia, cognitive abilities and school attendance [11, 15, 19, 20], although some of this evidence has recently been called into question [21–23].

Following the administration of anthelmintic drugs, STH infections rapidly recur in the context of ongoing environmental contamination [24]. Therefore, to achieve sustainable control of STH infections, facilitating improvements in water, sanitation and hygiene (WASH) in order to interrupt the cycle of ongoing reinfection is thought to be important [25, 26]. The impact of adequate water and sanitation infrastructure, as well as good hygiene practice, on preventing enteric infections and diarrhoeal illness is widely understood [27–29]. Intervention studies and systematic reviews specifically examining the link between WASH components and STH infections show evidence, albeit not consistent, that access to improved water and sanitation, and exposure to health education or hygiene promotion, are associated with reduced odds of STH infection [30, 31] or reduced risk of reinfection following drug treatment [32–36].

The optimal strategy for delivery of integrated deworming and WASH approaches remains uncertain. Due to the heavy burden of STH morbidity in school-aged children, and the cost-effectiveness of using school-based infrastructure [37], the World Health Organization (WHO) guidelines have focused predominantly on school-aged children as major targets of anthelmintic drug programmes [14, 38], with more recent recommendations including preschool-aged children, women of child-bearing age and adults in high-risk occupations [16]. School-based deworming programmes have been widely advocated and have become a cornerstone of STH control [15, 16]. The London Declaration on Neglected Tropical Diseases (NTDs) in 2012 saw 600 million annual doses of anthelmintic drugs donated towards the control of STH in children [39], a step towards achieving the WHO target of 75% deworming coverage of at-risk preschool- and school-aged children by 2020 [16]. This has resulted in a large global scale-up of chemotherapy programmes targeting school- and preschool-aged children [40].

However, recent modelling studies have raised concerns about the impact of child-targeted control programmes on the transmission of STH in the wider community [41–44]. These studies suggest that targeted programmes may not significantly impact the overall level of transmission [41, 42] and that child-focused strategies may be ineffective in reducing the overall community burden of the disease, particularly in areas where hookworm infections are predominant [43, 44]. Therefore, expanding treatment programmes to the whole community may result in improved STH control [42]. Cost-effectiveness modelling has demonstrated that community-based drug administration programmes for STH control are highly cost-effective when compared with treatment of school-aged children only [44, 45].

Intervention studies examining the impact of one or more components of WASH on STH infections have been conducted, or are currently underway, both in schools [32–36] and in communities [46–49]; however, the relative merits of the two delivery strategies have not been discussed in the literature. Furthermore, to our knowledge, there are no studies which have directly compared school-based and community-based integrated WASH and deworming programmes. The (School) Water, Sanitation, Hygiene and Deworming for Worms ((S)WASH-D for Worms) study aims to contribute to this evidence gap by comparing an integrated approach focused on school children with an integrated community-based approach. This report describes the protocol of the (S)WASH-D for Worms pilot study, which is being conducted in preparation of a full-scale cluster-randomised controlled trial. This protocol has been developed using the SPIRIT 2013 guidelines (see Additional file 1) [50].

The objectives of this pilot study are as follows:To examine the feasibility and acceptability of conducting a trial that recruits school-aged children and implements distribution of deworming medications along with school- and community-based WASH programmes. Specifically,To determine the feasibility and acceptability of study procedures by estimating rates of participant consent, recruitment, participation in data collection and retentionTo determine the feasibility and acceptability of the WASH and deworming programme by observing completion, uptake and usageTo identify operational issues for consideration when planning the full-scale trialTo obtain the initial estimates of STH prevalence, infection intensity and nutritional indicators for the purpose of informing sample size calculation
To establish “proof of principle” (preliminary evidence) for our hypothesis that a community-based deworming and WASH intervention is more effective in reducing STH infections in children than an exclusively school-based approach, by comparing estimates of the impact of the interventions

## Methods

### Design

This pilot study is a two-arm, non-randomised cluster intervention study. The six participating clusters, each based around a local primary school, are located in Aileu and Manufahi municipalities of Timor-Leste. Three clusters comprise the “control” arm of the study: in these, a WASH programme is delivered to the primary school, and albendazole is distributed to the schoolchildren. The other three clusters comprise the “intervention” arm, in which a WASH programme is delivered to both the primary school and the community in which the school is located, and albendazole is distributed to all community members. The follow-up period for the pilot study is 6 months following the distribution of albendazole, which will allow sufficient time for STH reinfection to occur [24], and represents the follow-up interval planned for the full-scale trial, which will take place over a 2-year period. Figure 1 depicts a flow diagram for the pilot study. This pilot study is registered with the Australian New Zealand Clinical Trials Registry (registration number ACTRN12615001012561).

**Fig. 1 Fig1:**
[figure not shown]
Flow diagram of the pilot study

### Setting

Timor-Leste is placed 133rd out of 187 countries on the Human Development Index [51], with 31.5% of the population living in severe poverty and a further 21.4% living in near poverty [51]. Over 50% of children under 5 years of age suffer from stunting, indicating chronic malnutrition [52]. A national survey in 2012 showed an overall STH prevalence of 29% in school-aged children in Timor-Leste, with 26 and 30% prevalence in the Manufahi and Aileu municipalities, respectively [53].

Open defecation in rural communities poses significant health risks. In 2015, 73% of the rural households in Timor-Leste did not have access to improved sanitation facilities, and 39% did not have access to improved water supplies [54]. Furthermore, a UNICEF survey in 2011 reported that 35% of the primary schools in Timor-Leste did not have latrines, and 62% of schools did not have regular access to a water supply [55].

Improved water and sanitation facilities across rural areas of Timor-Leste has been highlighted as a priority by the government of Timor-Leste [56], and multiple non-governmental organisations (NGOs) are also working in Timor-Leste to provide rural communities with improved access to reliable protected water sources and sanitation facilities and to promote hygiene behaviour [57–61].

### Integrated STH control programme

The WASH programmes in the pilot study are implemented by partner NGOs working in Timor-Leste. In order to ensure that the WASH programme would be completed within the planned time frames, two partner NGOs were selected. Plan International Timor-Leste is the implementer of the school- and community-based WASH programmes in the intervention arm of the study. These programmes are being delivered as part of a 4-year EU-funded water and sanitation project (FED/2011/270-630). Cruz Vermelha Timor-Leste (CVTL; a partner of Red Cross Australia) is the implementer of school-based WASH programmes in the control arm of the study, which are being delivered as a special project within the Integrated Community Based Risk Reduction program, funded by the Australian NGO Cooperation Program (ANCP 777-PRG01-PRJ08).

#### School WASH programme

All study clusters receive a school-based WASH programme, which includes three of the following components:(A)Providing access to a protected source of water which will be available year-round. This involves the construction of a new water system where required or the development or rehabilitation of existing water systems to improve water supply to the schools(B)Providing access to sanitation, achieved through either the construction of new school latrines or rehabilitation of existing, non-functional school latrines. Latrines are built following the Timor-Leste WASH in schools guidelines, which provide standards for the construction of sufficient, gender-segregated, accessible, private, secure, clean and culturally appropriate toilets for schoolchildren and staff, including facilities for use by menstruating students and staff [62]. Toilets are designed so that they are hygienic to use and easy to clean. At study schools, pour-flush latrines are constructed (or rehabilitated). The latrine pits are lined with concrete rings, and the superstructures are built with concrete blocks for durability. Handwashing stations are also constructed(C)Improving hygiene behaviour through hygiene promotion sessions conducted at primary schools. These sessions focus on using latrines, handwashing with soap at key times and keeping the environment clean. Strategies to communicate these messages include the use of flip charts, banners and posters, as well as game-oriented activities and participatory demonstrations

#### Community WASH programme

In addition to the school-based WASH programme, the three intervention clusters also receive a WASH programme delivered at the community level, including the same three components:(A)Providing access to a protected primary source of water that will be available year-round. This involves the construction of a new water system, or rehabilitation of an existing one, and comprehensive training for community-based water committees about operation and maintenance(B)Access to improved sanitation, achieved by increasing the number of household latrines. Plan International Timor-Leste and its partners utilise the community-led total sanitation (CLTS) approach, which encourages all households to take responsibility for building and using their own household latrines, thus eliminating open defecation in their communities [63]. CLTS challenges community members to reflect on their defecation practices through a series of sessions collectively called “triggering” that include transect walks, mapping open defecation areas, calculating the amount of faeces produced daily by each household, explanations on faecal-oral disease transmission routes and costs of medical treatment for gastrointestinal illnesses. If triggering is conducted optimally, community members come to the realisation that they are consuming each other’s faeces. Finally, community members make an activity plan and pledge to build or repair their household toilets [63]. CLTS facilitators provide information and lead discussions around the types of latrines which could be built and local materials that could be used in their construction. The two most common types of latrines that are built are simple direct pit latrines and offset pit pour-flush latrines(C)Hygiene promotion, conducted at the community level by Plan International and its partner NGOs as well as village health volunteers. This involves regular house-to-house visits to promote construction and use of latrines, handwashing with soap at key times and treatment and storage of drinking water

#### Administration of albendazole

In control clusters, albendazole is distributed to school-aged children only, while in intervention clusters, albendazole is distributed to every eligible member of the community. This includes all community residents, except for children under 1 year of age and pregnant women in the first trimester, in line with the WHO guidelines [64]. All doses are given as a single oral dose of 400 mg albendazole (Albenza, GlaxoSmithKline, Research Triangle Park, NC), taken under direct observation of the field staff.

In control clusters, albendazole distribution occurs at the primary school on a day agreed with the head teacher, with the first round given following the completion of school latrines and water systems. In intervention clusters, albendazole distribution occurs both at the primary school, again on a day agreed with the head teacher, and house-by-house, over a period of 1 to 2 days, with the first round given once 80% of households have latrines, and following the completion of school latrines and water systems. In both arms of the study, a second round of albendazole will be given at follow-up 6 months later, following the collection of follow-up stool specimens from the study participants.

Albendazole is widely distributed in large mass drug administration programmes globally; side effects are minor [64]. Parents are advised to seek healthcare at the local community health centre if their child is unwell following drug distribution, and community health centres are notified of study activities during field visits.

### Study outcomes

The primary outcomes will be used to examine feasibility and acceptability (objective 1). Primary outcomes relating to study feasibility and acceptability in terms of recruitment and participation (objective 1A) are as follows: the proportion of eligible children whose parents provide informed consent; the proportion of eligible children who provide stool samples, complete questionnaires and undergo measurement of height, weight and haemoglobin; and the retention rate of participants between baseline and follow-up.

Primary outcomes relating to the feasibility and acceptability of the WASH and deworming programmes (objective 1B) are as follows: the proportion of children and eligible community members who receive albendazole; the time taken for the completion of the school WASH programmes in each study cluster; the time taken to achieve 80% household latrine coverage in each intervention cluster; the proportion of schools and households with latrines and access to a reliable source of improved water; the proportion of schools with handwashing stations; and the proportion of children who report using latrines and handwashing stations.

Secondary outcomes, which will be used to inform sample size calculation (objective 1D) and to examine the study hypothesis (objective 2), are as follows: 6-month cumulative incidence of infection with STH (*Ascaris* spp., *N. americanus*, *Ancylostoma* spp. and *T. trichiura*) at follow-up; mean intensity of STH infection (measured as average number of eggs per gramme of faeces) at follow-up; mean haemoglobin concentration; and four anthropometric indices: weight-for-age, height-for-age, weight-for-height and body mass index (BMI)-for-age *Z*-scores (to identify underweight, stunting, wasting and thinness, respectively). Cumulative incidence of STH infection is the planned primary outcome in the full-scale trial. It should be noted that the term “cumulative incidence” is used for simplicity, as cases diagnosed at follow-up will include both incident infections and prevalent infections not cured by albendazole, particularly in the case of hookworm and *T. trichiura* infections [65].

All outcomes (see Table 1) will be compared between control and intervention clusters.

**Table 1 Tab1:** Study outcomes

Primary outcomes	
Proportion of eligible children who:	Provide parental informed consent
	Provide stool samples
	Complete questionnaires
	Undergo measurement of height, weight and haemoglobin
Participant retention rates between baseline and follow-up (defined as the proportion of baseline participants who were retained in the study at follow-up)	
Proportion of children and eligible community members who take albendazole	
Time taken to complete school WASH programmes in each study cluster	
Time taken to achieve 80% household latrine coverage in each intervention cluster	
Proportion of schools and households with functional and clean latrines	
Proportion of children who report using household and school latrines	
Proportion of schools and households with access to a reliable primary source of improved water	
Proportion of schools with handwashing stations	
Proportion of children who report using handwashing stations at school	
Secondary outcomes	
Cumulative incidence of infection with:	*Ascaris* spp.
	*T. trichiura*
	*N. americanus*
	*Ancylostoma* spp.
Mean intensity of infection (calculated as the average number of eggs per gramme of faeces) of:	*Ascaris* spp.
	*T. trichiura*
	*N. americanus*
	*Ancylostoma* spp.
Mean haemoglobin concentration	
Weight-for-age (underweight) *Z*-score	
Weight-for-height *Z*-score (wasting)	
Height-for-age *Z*-score (stunting)	
Body mass index (BMI)-for-age *Z*-score (thinness)	

### Selection and recruitment of clusters

Because each of the two partner NGOs only had capacity to conduct the WASH programme in one of the study arms within the required study time frame, and operated in neighbouring but different administrative areas, a randomised design could not be used for the pilot project. In the full-scale study, the intention is to randomise communities to the intervention and control arms.

For the pilot study, communities were considered eligible if they contained a primary school which was suitable for a school-based WASH programme (i.e. did not have access to functional improved latrines) and were located in a village with low sanitation coverage (i.e. less than 50% of households with latrines). Communities were selected in consultation with the implementing partner NGOs, based on their upcoming activities which fit into the study time frame.

Members of the (S)WASH-D for Worms research team accompanied NGO staff to community meetings in each cluster. For intervention communities, this occurred at the community “triggering”, and for control communities, this was a pre-arranged meeting with community and school leaders to explain plans for the school-based WASH programme. In all clusters, the study was explained to the village leader and head of school, who provided consent for the study activities to take place in their community. During the triggering in intervention communities, trial staff were also given the opportunity to explain the research study to the community. Following these initial meetings, plans were made for the research team to return for baseline data collection at the schools, within 1 to 3 weeks of the first meeting and prior to the commencement of the WASH programme.

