### Analysis

For the primary outcomes, analyses will be mainly descriptive. The proportions of eligible participants who gave informed consent and participated in each aspect of data collection will be calculated (with 95% confidence intervals (CIs)) and compared across the two study arms, at both baseline and follow-up, and will also be examined separately by gender and age group. The proportion of baseline participants retained at follow-up will also be calculated and compared across the study arms. Descriptive statistics will be used to examine the completeness of data collected using the study questionnaires.

The proportion of children and eligible community members who received albendazole, the proportion of schools and households with access to various WASH components and the proportion of children who report using various WASH components will be calculated (with 95% CIs) and compared across the two study arms, at both baseline and follow-up. The time taken to complete the school and community WASH programmes will be examined using descriptive statistics (mean, median, range).

For the secondary outcomes, prevalence at baseline and cumulative incidence at follow-up will be calculated (with 95% CIs) for each STH as will the mean and standard deviation of the infection intensity, expressed as eggs per gramme of faeces. Mean and standard deviation of the haemoglobin concentration and *Z*-scores for the four anthropometric indices will also be calculated. These outcomes will be compared across both arms of the trial using mixed effects multivariable regression models that account for clustering of participants within schools and villages. Cumulative incidence of infection will be modelled using multivariable Bernoulli logistic regression, with age and sex entered as covariates, baseline infection status as a fixed effect, and school and village as random effects. The study arm will be entered as a binary fixed effect to estimate differences in cumulative incidence between the study arms, using a cumulative incidence ratio (CIR). Intensity of infection will also be modelled with random and fixed effects as described above. Mixed effects linear regression will be used to model anthropometric *Z*-scores and mean haemoglobin concentration. Stata software will be used for all analyses (StataCorp LP, College Station, TX).

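### Baseline is said to precede the WASH programme, but in intervention clusters it followed CLTS triggering, so household latrine and defecation items there cannot be assumed to be pre-intervention

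*Protocol article*

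**What the plan says.** Selection and recruitment of clusters describes one sequence for both arms: an introductory meeting, then baseline. The meeting differed by arm. "For intervention communities, this occurred at the community “triggering", whereas "for control communities, this was a pre-arranged meeting with community and school leaders to explain plans for the school-based WASH programme". Baseline came next: "Following these initial meetings, plans were made for the research team to return for baseline data collection at the schools", to happen "within 1 to 3 weeks of the first meeting and prior to the commencement of the WASH programme".

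The Community WASH programme section lists three components delivered only in intervention clusters. Component B is household sanitation by the CLTS approach. It describes triggering as part of that approach: "CLTS challenges community members to reflect on their defecation practices through a series of sessions collectively called “triggering". The description ends with a commitment to act: "Finally, community members make an activity plan and pledge to build or repair their household toilets".

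The same recruitment section adds, for one arm only: "During the triggering in intervention communities, trial staff were also given the opportunity to explain the research study to the community". In all clusters the village leader and head of school were briefed and gave their agreement.

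Under Analysis, "the proportion of children who report using various WASH components will be calculated (with 95% CIs) and compared across the two study arms", at baseline as well as at follow-up. Consent and participation are compared between arms in the same way.

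**The concern.** Triggering cannot be inside the programme in one section and before its start in another. Under CLTS, households build their own latrines, and triggering is the step described as moving them to do so. A baseline taken after it follows the start of component B in the intervention arm, while the control-arm baseline follows only a briefing of leaders.

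The affected items feed primary outcomes: the proportion of households with latrines and the proportion of children who report using them. The child questionnaire asks about household latrine presence and use and about defecation practices. Early building could shift the answers, and so could changed reporting after sessions that challenge open defecation. Someone relying on the recruitment section would read these values as the state before any intervention. Time to 80% household latrine coverage is also a primary outcome, and the article gives it no start point.

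**Working it through.** The main question is the order of events, so the passages are set side by side.

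1. **Is triggering part of the programme?** Yes. Community WASH programme places it within component B.
2. **When did the research team first meet intervention communities?** At the triggering (Selection and recruitment of clusters).
3. **When was baseline?** After that meeting, at a planned interval of 1 to 3 weeks.
4. **Hence, in intervention clusters:** programme activity (triggering), then baseline. The same sentence says baseline came before the programme commenced. The two agree only if commencement means construction or some later activity, which the text does not say.
5. **In control clusters:** planning meeting with leaders, then baseline, then the school programme. No behaviour-change content is described for that meeting, so there is no conflict.

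**Which baseline items are exposed?** As described, triggering covers defecation practices, mapping of open defecation, transmission routes and a pledge about household toilets. That bears on household latrine presence, latrine use and defecation practices. It builds nothing at schools and no water system. Handwashing promotion belongs to component C, and the handwashing outcome concerns stations at school.

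**Time to 80% coverage.** If the clock starts at triggering, the recorded time equals the time counted from baseline plus 1 to 3 weeks (7 to 21 days). The recruitment wording points to a start after baseline and the component B description to a start at triggering.

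**Consent.** The article's figure reproduces: 522/602 = 0.867, which rounds to 87%. Not recruited: 602 − 522 = 80 = 39 absent + 41 present without a parent attending. Among children present: 522/(602 − 39) = 522/563 = 92.7%. No counts by arm are given. To show how little the pooled figure settles, assume two arms of 301 with the 39 absences split evenly (19.5 each):
- all 41 non-attending parents in one arm: (301 − 19.5 − 41)/301 = 79.9% against (301 − 19.5)/301 = 93.5%;
- the 41 split evenly: 86.7% in both.

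With 40% to 60% of the children in one arm and absences proportional, the first case gives 76% to 82% against 93.5%. These are bounds under assumptions. The documents do not say where the study lies between them, or that triggering had any part in it.

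**The case against.** The strongest reply is that this is a wording slip. Commencement may have meant construction, baseline is already complete, and the pilot is openly non-randomised, with a different NGO and area in each arm. Results are to be presented as proof of principle rather than causation. The primary analyses are mainly descriptive and compare arms at each time point. No change-from-baseline estimate is specified, and the infection models adjust for baseline infection, age and sex, not for baseline WASH. All of this is correct, and it limits the consequence. It does not remove the contradiction, nor the fact that the between-arm comparison at baseline is itself planned for these items.

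Three stronger readings are tempting, and the documents do not support them.

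- *All baseline WASH values and consent rates are non-comparable because of triggering.* School latrines, school handwashing stations and water sources are not shown to be affected. Consent used the same school parent meeting in all clusters, with no refusals among parents who attended. All losses were child absence or parent non-attendance. Consent is also listed as a measure of study procedures, not of acceptability of the WASH programme. What remains is that prior community-level explanation is described for one arm only. It could act through parents' attendance, and how many people heard it is not stated.
- *The baseline is inflated by a known amount.* A linear rise from 50% to 80% over 3 to 12 months would give 30 × 1/52 = 0.6 to 30 × 3/13 = 6.9 percentage points. The duration and the even pace are assumptions found nowhere in the article, and 50% is an eligibility ceiling for the village, not a measured starting value.
- *The programme's gain is understated.* That follows only if someone computes a change from baseline and if triggering had already moved the answers. The article shows neither.

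**Conclusion.** The point holds in limited form. For intervention clusters, the statement that baseline preceded the WASH programme conflicts with the article's own description of that programme. Baseline values for household latrine presence, latrine use and defecation practices in that arm cannot be assumed to be pre-intervention, and the control arm has no matching exposure. Direction and size are unknown, because no arm-level baseline values or triggering dates are given. The one quantity that can be stated is the 1 to 3 weeks of ambiguity in time to 80% coverage, which rests on the planned interval having been kept.

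The point should be corrected, because it affects how primary outcomes are read and costs almost nothing. It does not undermine the follow-up comparison or the infection analyses. Comparability of the arms is already limited by the non-randomised design; this is a separate matter of when one arm was measured.

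**What to change.** 1. Correct the sentence in Selection and recruitment of clusters so that programme start in intervention clusters is the triggering date. If the dates bear it out, add that baseline preceded construction.
2. Report the triggering date and the baseline date for each cluster.
3. Label the household latrine and defecation items at baseline as post-triggering in the intervention arm. Do not read the baseline comparison, or any baseline-to-follow-up change, for these items as starting from an unexposed state.
4. Start the clock for time to 80% household latrine coverage at triggering.
5. When reporting consent by arm, note that prior community-level explanation of the study is described only for the intervention arm.
6. Keep the questionnaire as the baseline measure. The under-50% eligibility figure should not replace it: that criterion applies to the village, its method and date are not described, and using it would change both unit and instrument between time points.
7. In the full-scale trial, collect baseline before triggering.

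For the pilot the cost is wording and a set of dates, assuming field records hold them. The downside is that the intervention-arm household baseline is presented as less clean, and time to 80% coverage comes out 1 to 3 weeks longer than if counted from baseline.
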